**4. VISIT IV: INTERVENTION STUDY INTERIM VISIT AT +3 MO**

Subjects will return to the clinic 3 months after starting on treat-to-target regimen plus either metformin or placebo for study follow up visit which will involve the following:

*Anthropometric measurements*: height, weight, waist circumference will be obtained. Vital signs and fasting glucose level will be checked. A venous catheter will be inserted in the antecubital fossa and blood sample will be drawn for fasting lipids, leptin, adiponectin, A1c, hepatic function tests, serum creatinine, and 25-hydroxyvitamin D.

*Vital Signs:* Blood pressure and pulse will be measured using an electronic sphygmomanometer.

*Anthropometric Measurements:* Weight, height and waist circumference will be measured in all participants. Weight will be measured using an electronic scale with patient donning under-garments and a hospital gown. Values will be expressed to the nearest 0.1 kg. Height will be measured using a wall-mounted Harpenden stadiometer. Waist circumference will be measured at the level of the umbilicus, using a standard measuring tape. All measurements will be done in triplicates and the average taken. We will derive body mass index from the weight and height data.

*Blood samples:* At 3 mo, following an overnight fast, we will draw fasting blood samples for the following laboratory tests: lipid profile, leptin, adiponectin, hemoglobin A1c, and 25-hydroxyvitamin D. These analytes will be redrawn at 6 and 9 months. Only 2 teaspoons of blood will be drawn for these tests at each time point. All samples will be spun upon collection using a centrifuge and the serum collected and stored at -70 degrees until assay.

Urine pregnancy test will be obtained on all female participants and will be repeated at + 6mo.

*Review of Glucose Data:* A pediatric endocrinologist will review patient’s glucose log book and glucometer and make necessary adjustments to insulin doses.

*Nutrition Evaluation:* A registered dietician will meet with the patients and his/her family and review patient’s interim dietary and make needed recommendations.

**5. VISIT V: INTERVENTION STUDY VISIT AT +6 MO**

**Visit V is identical to visit IV.**

**6. VISIT VI: STUDY CONCLUSION AT +9 MO**

At study conclusion, all subjects will return to the clinic in a fasting state for a final vital signs assessment, anthropometric measurements, physical examination, review of dossettes (pill counters), and a fasting blood draw for lipid profile, leptin, adiponectin, hemoglobin A1c, hepatic function tests, serum creatinine, and 25-hydroxyvitamin D as detailed below:

Subjects will return to the clinic 9 months after starting on treat-to-target regimen plus either metformin or placebo for end of study visit which will involve the following:

*End of study History and Physical Examination*: This discharge history and physical examination will focus on excluding any adverse effects from the study, and to establish endpoint anthropometric data: height, weight, waist circumference, and body mass index.

*Physical Examination*: height, weight, waist circumference will be obtained. Vital signs and fasting glucose level will be checked. A venous catheter will be inserted in the antecubital fossa and blood sample will be drawn for fasting lipids, leptin, adiponectin, HbA1c, hepatic function tests, serum creatinine, and 25-hydroxyvitamin D.

*Vital Signs:* Blood pressure and pulse will be measured using an electronic sphygmomanometer.

*Physical Examination (procedure):* Weight, height and waist circumference will be measured in all participants. Weight will be measured using an electronic scale with patient donning under-garments and a hospital gown. Values will be expressed to the nearest 0.1 kg. Height will be measured using a wall-mounted Harpenden stadiometer. Waist circumference will be measured at the level of the umbilicus, using a standard measuring tape. All measurements will be done in triplicates and the average taken. We will derive body mass index from the weight and height data.

*Blood samples:* At 9 mo, following an overnight fast, we will draw fasting blood samples for the following laboratory tests: lipid profile, leptin, adiponectin, and 25-hydroxyvitamin D. Only 2 teaspoons of blood will be drawn for these tests at each time point. All samples will be spun upon collection using a centrifuge and the serum collected and stored at -70 degrees until assay. Whole blood samples will be collected for HbA1c estimation. We will also obtain hepatic function tests and serum creatinine to compare the results to the screening and monitoring hepatic and kidney function studies to determine if there has been any effect of metformin use on participants’ hepatic and renal functions. One teaspoon of blood will be collected for this additional study.

*Urine Sample:* A spot urine sample will be collected for microalbumin and creatinine at study conclusion.

*Review of Glucose Data:* A pediatric endocrinologist will review patient’s glucose log book and glucometer and make necessary adjustments to insulin doses. This will conclude the study.

*Nutrition Evaluation:* A registered dietician will meet with the patients and his/her family and review patient’s interim dietary and make needed recommendations.

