**2. GENERAL STATEMENT OF PROBLEM**

Purpose: Include concise hypothesis to be tested by proposed research.

The significance of this project is to investigate the effects of adjunctive metformin therapy in children and adolescents with double diabetes.

There is a paucity of data on the role of adjunctive metformin therapy in children and adolescents with double diabetes. To help fill this knowledge gap, we propose a randomized, double-blind, placebo-controlled trial to evaluate changes in hemoglobin A1c (HbA1c) and anthropometry in patients with a diagnosis of type 1 diabetes who also have features of type 2 diabetes or metabolic syndrome as well as patients with type 2 diabetes who possess diabetes-associated autoantibodies. This will help determine the safety profile, and efficacy of adjunctive metformin therapy in these subjects.

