**Subject Replacement:** To ensure adequate sample size to reach significance according to our power calculations, we will oversample by 25% for each arm of the study. This will enable adequate numbers despite predicted study attrition.

**Statistical analyses** will be conducted so as to capture both the absolute changes in serum values for the proposed outcomes, as well as “time-to-event” information allowing us to compare the 2 groups with maximum efficiency.

1) **H1A**: Metformin supplementation of treat-to-target insulin regimen of diabetes care will have an influence on levels of HbA1c over time.

Mean levels of HbA1c will be computed at each time point, applying arcsine transformation to approximate Normality. 95% Confidence Intervals (95% CI) will be constructed around these estimates. All results will be graphed for visual appreciation of possible trends. Consecutive HbA1c levels for patients with and without metformin will be compared using repeated-measures Analysis of variance (ANOVA). Analyses of Covariance will be modeled to account for possible confounding due to gender and age. Similar analyses will be applied to the FPG levels, using the logarithmic transformation instead.

2) **H1B**: Patients randomized to adjunctive metformin therapy will achieve a greater reduction in HbA1c and fasting plasma glucose than those on placebo.

Adjunctive metformin and placebo groups will also be compared using both a logistic model and an actuarial survival model for “time-to-event”, where the event of interest is the decrease of the HbA1c level to 8% or less, as the biological cutoff below which serum glucose levels are considered stabilized. Similar analyses will be applied to FPG levels.

3) **H1C**: Metformin supplementation of treat-to-target regimen of diabetes care will have a measurable influence on blood pressure, waist circumference, body mass index, lipid profile, leptin, adiponectin, and 25-hydroxyvitamin D.

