Mean values for each one of these outcomes will be computed at each time point, applying appropriate transformations where needed to approximate Normality. 95% CIs will be constructed around these estimates. All results will be graphed for visual appreciation of possible trends. Consecutive measurements for patients with and without metformin will be compared using repeated-measures Analysis of variance (ANOVA). Analyses of Covariance will be modeled to account for possible confounding due to gender and age. Non-parametric equivalent of statistical tests will be used where necessary.

4) **H1D**: Transition from standard insulin treatment to treat-to-target regimen will provide better diabetes care for all patients. (Please see Table 2 below for a detailed explanation of the protocol for patient-directed forced-titration regimen).

Mean A1c levels at the beginning (-3mo) and at the end (0 mo) of the run-in period in all patients will be compared to subsequent mean A1c levels in the placebo group, using repeated measures ANOVA. Necessary adjustments for possible confounders will be carried out as described above.

d. Does the study involve randomization?

| YesX |  | No |  |
| --- | --- | --- | --- |

**If yes**, please describe process.

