**Randomization:**

Randomization for this study will be done by the Investigational Drug Services (IDS) using www.randomization .com. Randomization will be 1:1 (metformin : placebo) and will be blocked for every 10 subjects. Pharmacy will maintain blinding information and PI will contact IDS for emergency unblinding. IDS is available 24 hours a day and 7 days of the week via pager. Call schedule is available on OurNet.

e. How long will each subject be enrolled in the study?

Twelve months.

f. Provide a *brief* overview of what participation in the study will mean to each participant in terms of what he/she will experience. Describe in order, each procedure, how long each procedure will take and how often each procedure will be performed. Include doses & route of administration of any drugs and whether the procedure or drugs would **always**, **sometimes** or **never** be required as part of the subject’s standard of care.

Methods and assessments:

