**3. VISIT III: BASELINE INTERVENTION STUDY VISIT AT O MO**

Following the screening study, qualified subjects will return to the Children’s Diabetes Service in the morning, after an overnight fast for initial intervention study blood draw. Anthropometric measurements: height, weight, waist circumference will be obtained. Vital signs and fasting glucose level will be checked. A venous catheter will be inserted in the antecubital fossa and blood sample will be drawn for fasting lipids, leptin, and 25-hydroxyvitamin D at baseline.

*Vital Signs:* Blood pressure and pulse will be measured using an electronic sphygmomanometer.

*Physical Examination:* Weight, height and waist circumference will be measured in all participants at baseline, 3 months and 6 months. Weight will be measured using an electronic scale with patient donning under-garments and a hospital gown. Values will be expressed to the nearest 0.1 kg. Height will be measured using a wall-mounted Harpenden stadiometer. Waist circumference will be measured at the level of the umbilicus, using a standard measuring tape. All measurements will be done in triplicates and the average taken. We will derive body mass index from the weight and height data.

*Blood samples:* At baseline, following an overnight fast, we will draw fasting blood samples for the following laboratory tests: lipid profile, leptin, adiponectin, hepatic function tests, serum creatinine, and 25-hydroxyvitamin D. These analytes will be redrawn at 3, 6 and 9 months. Only 2 teaspoons of blood will be drawn for these tests at each time point. All samples will be spun upon collection using a centrifuge and the serum collected and stored at -70 degrees until assay. Whole blood samples will be collected for HbA1c estimation.

Urine test: Urine pregnancy test will be obtained on all female participants and will be repeated at +3mo, and + 6mo.

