**Assessments for Safety**

**Hypoglycemia**: The major safety concern for this study, as in the general management of diabetes, is hypoglycemia. For this study, the following classification of hypoglycemia will be used: (a) **major**: hypoglycaemic event requiring a third party assistance, (b) **minor**: self measured plasma glucose level of ≤ 60 mg/dL, (c) **symptoms only**: self-measured plasma glucose of > 60 mg/dL or no measurement during the episode, (d) **nocturnal**: self-measured plasma glucose of ≤ 60 mg/dL occurring between 11 pm and 6 am. Hypoglycemia will be monitored by self-measured plasma glucose by checking blood glucose before meals, at bedtime, and at 3 a.m. We will evaluate the glycemic profile every third day by reviewing the data sent in to our office by the participants’ families via fax or email. Insulin dose adjustments, and other appropriated suggestions will be made based on these data. We will ensure that participants maintain a bedtime blood glucose level of >100 mg/dL before going to sleep. It is the standard of care for patients to check their blood sugar level before bed and if it is less than 100 mg/dL to eat a snack and recheck their blood sugar to make sure that it is over 100 before going to bed.

Participants will also check 3AM blood glucose twice weekly and also on 2 consecutive nights following changes to their long-acting insulin dose.

**Renal and liver function tests**: We will obtain liver function studies, and creatinine levels at the beginning and at the end of the study.

We will monitor **weight, body mass index, and vital signs** at each visit.

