As the safety officer [name] will monitor participants in the study for adverse events related to the study drug, and make recommendations regarding removing subjects from the study or terminating the study if the incidence of adverse effects is significant.

He will review unblinded study data every month for the first 3 months of the study, and then every three months thereafter with regards to assignment of subjects to the study arms, prevalence of gastrointestinal side effects (including nausea, diarrhea and abdominal discomfort), unusual weight loss (>10% of body weight in 3 months), admissions to hospital or elevation of liver enzymes to >3 times above the normal limit. He will also review all other SAEs. This information will be forwarded to him by the study coordinator, and unblinding information by Investigational Drug Services which is responsible for blinding the study drug. He will perform this review every 3 months until the completion of the study. If an issue is found, he will report this promptly to the PI and will jointly issue an adverse effects or SAE report (as the case may be) with the PI to the UMass IRB and the study sponsor, Novo Nordisk Inc.

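### The effect of metformin on liver and kidney function is to be judged by comparing month 9 with earlier values, which cannot separate metformin from changes common to both arms; no between-arm estimate is planned for these tests

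*Protocol*

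**What the plan says.** The general statement of the problem (section 2) gives safety as one purpose of the placebo-controlled design: "This will help determine the safety profile, and efficacy of adjunctive metformin therapy in these subjects". Allocation is concurrent and balanced: "Randomization will be 1:1 (metformin : placebo) and will be blocked for every 10 subjects".

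Under Visit VI, Blood samples, the stated use of the month 9 hepatic tests and creatinine is this: "compare the results to the screening and monitoring hepatic and kidney function studies to determine if there has been any effect of metformin use". The Assessments for Safety section says only when the tests are taken: "We will obtain liver function studies, and creatinine levels at the beginning and at the end of the study".

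The secondary hypothesis H1C states that metformin "will have a measurable influence on blood pressure, waist circumference, body mass index, lipid profile, leptin, adiponectin, and 25-hydroxyvitamin D". For these outcomes the arms are compared directly: "Consecutive measurements for patients with and without metformin will be compared using repeated-measures Analysis of variance (ANOVA"). Hepatic tests and creatinine are in neither this list nor the outcome list in the sample size section.

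The tests are nevertheless drawn in everyone at month 0, where the Visit III sample covers "lipid profile, leptin, adiponectin, hepatic function tests, serum creatinine, and 25-hydroxyvitamin D", with redraws at months 3, 6 and 9.

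In section 8 a safety officer reviews unblinded data "with regards to assignment of subjects to the study arms". The hepatic item in that review is an elevation of liver enzymes to more than 3 times the normal limit. Kidney function is not listed.

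**The concern.** The Visit VI sentence gives a question (has metformin affected liver or kidney function?) and a comparison meant to answer it (month 9 against earlier values). The two do not match. A later-versus-earlier comparison asks whether values have changed. It isolates metformin only if nothing else would have changed them, and this protocol gives reasons to expect other change.

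If the sentence is followed as written, two errors are possible. A shift shared by both arms could be reported as an effect of metformin. A real effect could also be hidden by a shared shift in the opposite direction. The Background says the long-term side effects of metformin in young people with type 1 diabetes are unknown, so either error would weaken a finding the trial is meant to supply. The randomised placebo arm, sampled at the same visits, removes the shared shift, but no analysis of these tests uses it for that purpose.

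**Working it through.** **Step 1. Does the stated comparison isolate metformin?** Write D for the mean change from the earlier value to month 9 that occurs without metformin, and M for the effect of metformin.

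- Change in the metformin arm: D + M
- Change in the placebo arm: D
- Change with both arms combined at 1:1: D + M/2
- Difference between arms: (D + M) − D = M

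Only the last line equals M whatever D is. The first equals M only if D = 0.

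**Step 2. Does the protocol give reasons for D to differ from 0?** It gives three.

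- *Insulin.* Treat-to-target titration starts in every participant at month 0 (Visit III, Procedure).
- *Time.* Screening is at month −3 and the last visit at month +9, so the span is 12 months, in participants enrolled at Tanner stages 2 to 5.
- *Selection.* Those with abnormal liver or kidney tests at screening are not enrolled (Visit I). Values selected to be normal can be expected to drift back toward the population mean on retesting, in both arms.

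**Step 3. Does another section supply the between-arm contrast?**

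| Place in protocol | Hepatic tests / creatinine compared between arms? |
| --- | --- |
| Outcome list, sample size section | Neither listed |
| H1A, H1B | HbA1c and fasting glucose only |
| H1C | Neither listed |
| H1D | HbA1c only, run-in against later values in the placebo group |
| Assessments for Safety | Timing only |
| Safety officer's review, section 8 | Unblinded, but liver enzymes by threshold; creatinine not listed |

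None gives an estimate of M for these tests.

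**Step 4. How large could the error be?** The protocol states no figure for this comparison, so there is none to reproduce. It gives no drift, SD or effect size for any liver or kidney test, and it names no test. The following is an illustration under assumptions.

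- *From the protocol:* two-sided 5% level; 29 per arm as calculated; 74/2 = 37 per arm as randomised.
- *Assumed:* a paired t-test for the before-after comparison; drift d in SDs of the change; equal SDs in the two arms.
- *Formulas:* the rejection rate comes from the noncentral t distribution. Noncentrality is d√n on n − 1 degrees of freedom for the metformin arm alone, and d√(2n) on 2n − 1 for both arms combined. For a between-arm difference of δ SD it is δ√(n/2) on 2n − 2.
- *Example:* n = 29 and d = 0.3 give noncentrality 0.3 × √29 = 1.62 and a rejection rate of 34.5%.

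Rejection rates with no metformin effect (n = 29 to n = 37 per arm):

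| Assumed drift | Before-after, metformin arm | Before-after, arms combined | Between arms |
| --- | --- | --- | --- |
| 0 | 5% | 5% | 5% |
| 0.2 SD | 18–22% | 32–40% | 5% |
| 0.3 SD | 35–43% | 61–72% | 5% |
| 0.5 SD | 74–84% | 96–99% | 5% |

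*Masking.* Suppose a true effect of 0.5 SD and a shared drift of −0.3 SD.

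- Metformin arm alone: the net change is 0.5 − 0.3 = 0.2 SD, detected 18–22% of the time.
- Arms combined: the net change is 0.25 − 0.3 = −0.05 SD, declared significant about 6–7% of the time and in the wrong direction.
- Between arms: noncentrality is 0.5 × √(29/2) = 1.90, or 0.5 × √(37/2) = 2.15, giving detection of 47–56%.

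**Step 5. What can the between-arm comparison show?** The difference detectable with 80% power is about (1.96 + 0.84) × √(2/n): 0.74 SD at n = 29 and 0.65 SD at n = 37. A 0.5 SD effect would be missed about 44–53% of the time, so a non-significant result would not show that there is no effect.

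**The case against.** The strongest reply is that the Visit VI sentence is a sampling instruction. It explains why extra blood is drawn and names no test, estimand or analysis set. Any between-arm analysis of change would need the same earlier values, and a statistical analysis plan could add one. The analysis of safety laboratory values is often left to that document.

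Part of this stands. The sentence does not exclude a comparison by arm, and leaving safety tests out of H1C would not be an error by itself. But the sentence does more than schedule a sample: it says which comparison will determine the effect of metformin, and that comparison cannot do so. A later plan could add the right contrast, but this sentence would still need correcting.

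Four stronger readings are tempting, and the documents do not support them.

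- *The placebo arm is unused for liver safety.* The safety officer sees unblinded data by arm, including liver enzymes above 3 times the limit. What is missing is an estimate of effect, and any listed review of creatinine.
- *The protocol prescribes a paired test on each participant's own values.* That is a natural reading, but neither the test nor the phrase is in the text.
- *Screening is the only baseline.* The sentence also names monitoring values, which can include the month 0 draw.
- *Every participant changes insulin at month −3.* The conversion rule is for those on another long-acting insulin, and some may already use detemir and aspart. The change shared by all is treat-to-target titration from month 0.

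**Conclusion.** The point holds as a wrongly stated contrast. The only comparison the protocol offers for determining the effect of metformin on hepatic and renal function cannot separate it from changes common to both arms, and no between-arm estimate is planned in the document. This conclusion follows from the design and does not depend on any assumed number.

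The size of the error in this trial is unknown. The 18–22%, 35–43% and 74–84% rejection rates rest wholly on assumed drifts of 0.2, 0.3 and 0.5 SD and an assumed paired test. A reader might take them as the trial's expected false-positive rates, but the protocol contains nothing from which to estimate the drift. If drift were zero, the before-after test would keep its 5% level.

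Severity is minor to moderate. These are safety measures outside the stated primary and secondary aims, and the primary HbA1c comparison is not affected.

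**What to change.** In Visit VI, Blood samples, replace the comparison with text on these lines:

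> The effect of metformin on hepatic function tests and serum creatinine will be estimated as the metformin-minus-placebo difference at month 9, adjusted for the month 0 value, with a 95% confidence interval. A non-significant difference will not be read as absence of an effect. Comparison with a participant's own earlier values will be used for individual safety monitoring only.

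Refer to the same analysis under Assessments for Safety. No rule for concluding absence of harm from a confidence limit should be added: the protocol sets no margin, and one upper limit would not suit every analyte in a hepatic panel.

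The cost is a few sentences. Both arms already have these tests at months 0 and 9, so no visits, blood samples or participants are added. If a statistical analysis plan exists, check that it carries the same contrast.
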